# A prospective pilot study of home monitoring in adults with cystic fibrosis (HOME-CF): protocol for a randomised controlled trial

**DOI:** 10.1186/s12890-017-0366-x

**Published:** 2017-01-23

**Keywords:** Cystic fibrosis, Home monitoring, Pulmonary exacerbations, Health related quality of life, Health economics

## Abstract

**Background:**

Home monitoring has the potential to detect early pulmonary exacerbations in people with cystic fibrosis (CF), with consequent improvements in health outcomes and healthcare associated costs. This study aims to assess the effects of home monitoring on hospital admissions, quality of life, antibiotic requirements, exacerbation frequency, lung function, nutritional outcomes, anxiety, depression, costs and health outcomes, as well as the qualitative effects on the patient experience.

**Methods:**

This randomised controlled mixed-methods trial aims to recruit 100 adults with CF cared for in one large regional CF centre. Participants are randomly allocated 1:1 to the intervention group (twice-weekly home monitoring of symptoms measured by the Cystic Fibrosis Respiratory Symptom Diary – Chronic Respiratory Infection Symptom Score (CFRSD-CRISS) and Forced Expiratory Volume in one second (FEV_1_)) or a control group (routine clinical care) for the 12-month study period. Measurements are recorded at study visits at baseline, 3, 6, 9 and 12 months. Spirometry, body weight, co-morbidities, medications, hospital inpatient days, courses of antibiotics (oral and intravenous), pulmonary exacerbations (defined by the modified Fuchs criteria) are recorded at each study visit. Health status, capability and health economics are measured at each study visit by the Hospital Anxiety and Depression Scale (HADS), the ICEpop CAPability measure for Adults (ICECAP-A), EuroQol 5 dimensions (EQ-5D-5L) questionnaire and an adapted resource use questionnaire. The patient experience is assessed by semi-structured qualitative interviews at baseline and 12 months.

**Discussion:**

Results from this study will help to determine the effect of home monitoring on inpatient bed days and quality of life in adults with CF, as well as other relevant health and health economic outcomes.

**Trial registration:**

This study protocol is registered with Clinicaltrials.gov (NCT02994706), date registered 16^th^ July 2014

## Background

Cystic fibrosis (CF) is the most common fatal inherited condition in Caucasians, affecting more than 10,000 people in the UK [1] and at least 70,000 people worldwide [2]. CF is caused by abnormal function of the cystic fibrosis transmembrane conductance regulator (CFTR), a complex protein which functions primarily as a chloride channel, regulating movement of ions and fluid across epithelial surfaces [3]. CFTR dysfunction causes epithelial secretions to be abnormally dehydrated and viscous, resulting in damage to several organs including the lungs, pancreas, intestines and liver. Within the lungs, chronic infection and inflammation results in progressive lung disease and premature death due to respiratory failure. Survival in CF has dramatically improved over the last 40 years due to factors including improvements in antibiotic therapy, better nutrition and the development of centres devoted to the provision of specialised CF care. As a result, CF has changed from a predominantly paediatric disease to the current situation where the majority of individuals with CF survive into adulthood. The median predicted survival in the UK is currently in excess of 45 years of age [1] and that of people with CF born in the year 2000 is predicted to be in excess of 50 years of age [4].

People with CF often experience a burden of symptoms on a daily basis, typically including: cough, sputum production, wheeze, breathlessness, chest tightness and fever [5]. When patients develop worsening symptoms, they are advised to contact their CF multidisciplinary team (MDT) and may be diagnosed with a pulmonary exacerbation. Pulmonary exacerbations are typically treated with antibiotics targeted at the bacteria that cause chronic infection in that individual patient. However, symptoms of a pulmonary exacerbation do not usually develop suddenly, but instead worsen slowly over the course of several days to weeks. Patients presenting with less severe symptoms are more likely to receive a course of oral antibiotics, but as the exacerbation worsens the patient may require intravenous antibiotics. Intuitively, it would be expected that if the patient were diagnosed with a pulmonary exacerbation earlier, with milder symptoms, the requirement for intravenous antibiotics would be less.

Anecdotally we know that some patients are able to perceive a change in their symptoms better than others. Some realise that they are developing an exacerbation early on, whereas others present when they have already become more severely unwell. Additionally, patients may know that they are developing an exacerbation, but are unable to come to clinic due to other commitments or due to a lack of clinic capacity. In either case, we suspect that if we were able to diagnose the exacerbation at an earlier stage we may be more likely to be able to treat it successfully with a course of oral antibiotics, rather than intravenous antibiotics. Additionally, in our experience if the patient is less unwell they are more likely to be able to receive intravenous antibiotics at home, rather than requiring admission. This could potentially be beneficial to the patient, preventing the complications of a more severe infection and could also reduce healthcare expenditure by averting a hospital admission.

Several previous studies have assessed the effect of telehealth or home monitoring in people with CF, but the vast majority of these studies have been small feasibility studies with limited external validity [6–13]. A randomised pilot study in CF patients demonstrated that home monitoring was able to detect more pulmonary exacerbations than standard care [14]. A large randomised controlled study of home monitoring is currently ongoing in the USA, assessing the primary outcome of change in forced expiratory volume in 1 s (FEV_1_) over a 12-month period [15]. Secondary outcome measures include the effect of home monitoring on CF respiratory symptom scores, pulmonary exacerbations, health-related quality of life, treatment burden, change in prevalence of resistant strains of bacteria and adverse events. There are no cost-effectiveness analyses included in this study and no qualitative assessment of the patient experience.

The primary aims of the current study are to (1) determine whether home monitoring is effective compared with routine care in reducing hospital inpatient bed days; and (2) assess whether this results in differences in health-related quality of life over a 12 months period in adults with CF. We hypothesise that participants randomly allocated to home monitoring will require fewer hospital inpatient bed days and that they will have better health-related quality of life compared with those receiving routine care.

## Methods/Design

### Study design

This single-centre, non-blinded, randomised controlled mixed-methods trial will be conducted at West Midlands Adult CF Centre, Heart of England NHS Foundation Trust, Birmingham, UK.

### Participants

#### Inclusion/exclusion criteria

To be eligible for enrolment, participants must be able to give informed consent, be aged ≥ 18 years and have a diagnosis of CF confirmed by clinical characteristics, sweat test and/or genetic testing. They must be clinically stable at the time of recruitment (as assessed by the treating physician) and have a history of at least one admission to hospital to receive intravenous antibiotics over the preceding 24 months.

Exclusion criteria include: 1) currently participating in another clinical trial (excluding observational studies); 2) pneumothorax or lung surgery within the previous 3 months or eye surgery (e.g. cataract operation) in the previous 4 weeks (since these factors prevent measurement of spirometry); 3) airway infection with *Burkholderia cenocepacia* or *Mycobacterium abscessus* at the time of recruitment; 4) previous lung transplantation procedure.

### Sample size

Estimating the mean number of hospital inpatient days is 42 for those receiving standard care and 36 for those receiving monitoring, assuming a standard deviation of 10 and 40 patients per arm, approximate 95% confidence intervals for these estimates would be (39, 45) and (33, 39) respectively. To allow for patient drop out a total of 100 patients will be recruited (50 patients in each group).

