**Fig. 1 Fig1:**
[figure not shown]
Flow of patients through the study

Participants will be screened from the West Midlands Adult CF Centre database by the study investigators. If eligible, the study investigators will approach patients when they are attending routine clinic visits or during inpatient admissions to explain the study and if they are potentially interested they will be given the Participant Information Sheet. Having had time to consider the study and have any questions answered to their satisfaction, patients still keen to take part will be asked to provide written informed consent. It will be explained that they may withdraw from the study at any time.

At this point, baseline data will be obtained and the participant will be asked to take part in a semi-structured qualitative interview to assess the patient experience of their care to date and their expectations of participating in the study. Within strata, participants will then be randomly assigned to receive either home monitoring or routine care. The strata are based on the number of hospital admissions to receive intravenous antibiotics over the preceding 24 months, separated into four strata: ‘1–2 admissions’, ‘3–4 admissions’, ‘5–6 admissions’ and ‘more than seven admissions’. The randomisation will be completed by the selection of randomly ordered sealed opaque envelopes, with randomisation having been performed by a clerical member of the CF team with no knowledge of the study.

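### The bed-day standard deviation of 10 has no stated source and is very hard to reconcile with the entry rule and admission strata, so the stated ±3-day precision per arm is probably optimistic by a factor of about 1.5 to 3.5

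*Protocol article*

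**What the plan says.** The Sample size section bases the trial on the precision of each arm's mean: "Estimating the mean number of hospital inpatient days is 42 for those receiving standard care and 36 for those receiving monitoring". The spread and the evaluable number enter in a further clause, "assuming a standard deviation of 10 and 40 patients per arm". The section concludes that "approximate 95% confidence intervals for these estimates would be (39, 45) and (33, 39) respectively". Recruitment is then raised from 80 to 100 to allow for dropout. The section gives no source for the SD, no alternative value, no interval for the difference between arms, and no power, significance level or test.

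Two other places describe who enters:

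- Inclusion/exclusion criteria: patients must "have a history of at least one admission to hospital to receive intravenous antibiotics over the preceding 24 months".
- Recruitment and randomisation: four strata of admissions for intravenous antibiotics over the preceding 24 months, from 1–2 up to "more than seven admissions".

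Primary outcomes measures counts bed days as complete 24-hour periods, so zero is a possible value.

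**The concern.** An SD of 10 around a mean of 42 describes a fairly uniform population, with a coefficient of variation of 10/42 = 0.24. The entry rule and strata describe a mixed one. Annualised, past admission rates run from 0.5 to more than 3.5 a year, at least a sevenfold span. A patient with exactly one admission in 24 months had no admission starting in one of those two years. Bed days are also the sum of a few multi-day stays, so they vary by chance even between patients with the same underlying rate.

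This SD carries the only precision statement in the document. The two stated intervals just touch at 39, which suggests that a 6-day difference would be resolved fairly well. If the true SD is much larger, the estimate will be far less precise than readers were led to expect, and an inconclusive result could be taken as evidence of no effect. The Background section does state an aim of determining whether home monitoring reduces bed days.

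**Working it through.** **Inputs from the document:** means 42 and 36, SD 10, 40 per arm (Sample size); the entry rule; the four strata. The means are taken to cover the 12-month study period, which the Sample size section does not say.

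**Assumed inputs:** stratum midpoints of 1.5, 3.5, 5.5 and 8 admissions in 24 months, that is 0.75, 1.75, 2.75 and 4 a year (the last is a choice for an open-ended stratum); stratum mix; length of stay; Poisson arrival of admissions.

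**1. The stated intervals.** 1.96 × 10/√40 = 3.10, giving 38.9 to 45.1 and 32.9 to 39.1. These round to the stated figures. Allowing 20% dropout, 40/0.8 = 50 per arm, also as stated.

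**2. Share of patients with zero days, without a distributional model.** If a share p has zero days and all others are identical, the variance is 42² × p/(1−p), the smallest possible for that p. Setting this to at most 10² gives p ≤ 0.0567/1.0567 = 5.4%, about 2 patients in 40.

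**3. Chance variation alone.** With identical patients, Poisson admissions and a constant stay of L days, SD = √(42 × L).

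| Stay L (assumed) | Admissions per year, 42/L | SD |
|---|---|---|
| 2.38 | 17.6 | 10.0 |
| 7 | 6.0 | 17.1 |
| 10 | 4.2 | 20.5 |
| 14 | 3.0 | 24.2 |

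SD 10 therefore needs about 35 admissions in 24 months. Even if every patient were in the top stratum at 4 a year, L = 42/4 = 10.5 and SD = √(42 × 10.5) = 21.

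**4. Adding differences between strata, with the mean held at 42.** Let bed days be proportional to the past rate. The between-stratum SD is 42 × (SD of rates/mean rate), and the implied stay is 42/mean rate. Column A is √(between² + Poisson²). Column B is deliberately lenient: the between-stratum spread is cut to 30% and the Poisson variance to a quarter.

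| Mix of the four strata, % | Implied stay | Between SD | Poisson SD | A | B |
|---|---|---|---|---|---|
| 25/25/25/25 | 18.2 | 21.9 | 27.6 | 35.2 | 15.3 |
| 50/25/15/10 | 25.8 | 27.6 | 32.9 | 43.0 | 18.4 |
| 10/40/40/10 | 18.5 | 15.8 | 27.8 | 32.0 | 14.7 |
| 10/20/30/40 | 14.7 | 16.2 | 24.9 | 29.7 | 13.4 |

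The SD runs from about 13 to 18 under lenient assumptions and from about 30 to 43 under full ones. A working range of 15 to 35 is a judgement within these limits, not a derived figure.

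**5. Resulting precision at 40 per arm.** Per arm: 1.96 × SD/√40. Difference: 1.96 × SD × √(2/40).

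| SD | Per arm | Difference |
|---|---|---|
| 10 | ±3.1 | ±4.4 |
| 15 | ±4.6 | ±6.6 |
| 20 | ±6.2 | ±8.8 |
| 25 | ±7.7 | ±11.0 |
| 30 | ±9.3 | ±13.1 |
| 35 | ±10.8 | ±15.3 |

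The interval around an observed 6-day difference includes zero once SD exceeds 6/(1.96 × √0.05) = 13.7. Keeping all 50 per arm does not restore the stated precision: at SD 15 the per-arm half-width is still ±4.2.

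**The case against.** The entry rule and strata count past admissions for intravenous antibiotics over 24 months. The outcome is future bed days, and its definition is not limited to those admissions. Moving from one to the other needs a length of stay, a stratum mix, a link between past and future rates and an arrival model, and the documents supply none of them. If future rates keep only 30% of the past spread, the between-stratum SD with equal strata falls to 6.6. With patients only in the two middle strata it is 9.3. A source for the SD may also stand in the full protocol, which is not at hand.

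This stands to the extent that SD 10 is not logically excluded. A reader might infer that the entry rule and strata rule it out, and that the stated precision cannot be reached. The documents do not support that, because each step of the argument except the bound on zeros uses an assumed input. The counter-examples, however, cover only the between-stratum part. To keep the total at 10 in the first of them, within-patient variance would have to be at most (100 − 6.6²)/27.6² = 7% of the Poisson value, so admissions would have to be almost regular.

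A reader might also turn the larger SD into a loss of power. The trial is titled a pilot, claims no power, and calls its between-group tests exploratory, so there is no stated power to fall short of. Its reported intervals will come from the observed data, so a wrong planning SD will not bias them.

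**Conclusion.** The concern holds for the SD input, not for the calculation, which is correct. SD 10 at mean 42 has no stated source and is very hard to reconcile with the population the protocol describes. For an assumed SD of 15 to 35, the stated ±3-day precision per arm is optimistic by a factor of about 1.5 to 3.5, and at every SD in that range the interval for the difference is wider than ±6 days. The size depends on the assumed midpoints, mix, stay and arrival model; the bound of about 5% on patients with zero days does not. The consequence is a misleading statement of expected precision in a pilot. It is not an error in the analysis and not a reason to change the number recruited.

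**What to change.** Keep 100 patients and rewrite the Sample size paragraph:

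- Give the source of SD 10, or replace it with the SD of 12-month bed days among eligible patients at the centre. The protocol says the centre database is used for screening but not that it holds bed days, so this depends on what the records contain.
- Restate the per-arm 95% confidence intervals with that SD and add the interval for the difference between arms.
- Until that figure is available, show the range for assumed SDs of 15 to 35 at 40 per arm: ±4.6 to ±10.8 days per arm and ±6.6 to ±15.3 days for the difference, beside ±3.1 and ±4.4 at SD 10.
- State that at such SDs the trial estimates the effect but cannot reliably confirm or exclude a 6-day difference.

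The cost is a query of centre records, one rewritten paragraph, and a stated precision that looks less favourable.

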### Recruitment and randomisation

The flow of participants through the study will reflect the recommendations from the Consolidated Standards of Reporting Trials statement [16] and is outlined in Fig. 1. Participants will receive written and verbal information explaining the study and written consent will be obtained from all participants. West Midlands (Solihull) Research Ethics Committee (12/WM/0379) approved the study, Heart of England NHS Foundation Trust is the trial sponsor and the protocol is registered with Clinicaltrials.gov (NCT02994706).

**Fig. 1 Fig1:**
[figure not shown]
Flow of patients through the study

Participants will be screened from the West Midlands Adult CF Centre database by the study investigators. If eligible, the study investigators will approach patients when they are attending routine clinic visits or during inpatient admissions to explain the study and if they are potentially interested they will be given the Participant Information Sheet. Having had time to consider the study and have any questions answered to their satisfaction, patients still keen to take part will be asked to provide written informed consent. It will be explained that they may withdraw from the study at any time.

At this point, baseline data will be obtained and the participant will be asked to take part in a semi-structured qualitative interview to assess the patient experience of their care to date and their expectations of participating in the study. Within strata, participants will then be randomly assigned to receive either home monitoring or routine care. The strata are based on the number of hospital admissions to receive intravenous antibiotics over the preceding 24 months, separated into four strata: ‘1–2 admissions’, ‘3–4 admissions’, ‘5–6 admissions’ and ‘more than seven admissions’. The randomisation will be completed by the selection of randomly ordered sealed opaque envelopes, with randomisation having been performed by a clerical member of the CF team with no knowledge of the study.

## Interventions

### Routine care group

These participants will continue to receive routine CF care, including regular outpatient clinic appointments and inpatient admissions if required.

### Home monitoring group

Participants randomized to receive home monitoring will be provided with a Bluetooth-enabled digital spirometer and a ‘Microsoft Windows Mobile’ enabled mobile phone. Participants will be shown how to use the equipment before going home. Participants will be asked to record their FEV_1_ using a digital spirometer twice weekly (Monday and Thursday), which will take around 5 min to complete. Participants will also record their symptoms twice weekly (Monday and Thursday) on the mobile phone by completing the Cystic Fibrosis Respiratory Symptom Diary – Chronic Respiratory Infection Symptom Score (CFRSD-CRISS) [5]. This is a validated disease-specific tool (consisting of 16 questions) designed to detect symptoms of pulmonary exacerbations in CF, taking around 5 min to complete.

Data regarding lung function and symptoms will be automatically transmitted via a secure encrypted wireless connection and the research team will be able to access this data instantaneously on a specially designed website. The mean values of the first 2 weeks’ data will be used to determine the participants’ baseline levels for FEV_1_ and CFRSD-CRISS during the run-in phase. Following this initial 2-week period, the CF team will receive an email alert if participants’ FEV_1_ or symptoms deteriorate below a set threshold. The criteria that will trigger an email alert are one of: 1) a drop in FEV_1_ of 10% or more from baseline; 2) total score of the CFRSD-CRISS worsening by more than three points from baseline. Following an email alert, the CF team will contact the participant within 24 h to discuss their symptoms. Based on this discussion, the research team will advise the participant on the best management. If the participant needs to be assessed in the outpatient clinic, we will arrange the next available convenient appointment. Depending on the clinical assessment, participants will receive a course of antibiotics, either oral or intravenous depending on the severity of symptoms, sputum microbiology and patient choice. If prescribed antibiotics, we will document whether these were prescribed for a protocol-defined pulmonary exacerbation (see definition below).

To minimize lack of adherence to home monitoring, we will re-enforce the importance of adhering to the study protocol at each study visit. The system will alert the research team if any participant fails to record symptoms and spirometry data. If this occurs, we will call the participant to check if they are having any problems with the equipment and that they are willing to proceed with the study. If there are any difficulties with using the equipment, we will explain how to resolve this issue. If any participant fails to submit data for more than 20% of occasions over any 28-day period we will advise them that they risk being withdrawn from the study. If there was a good reason for them not to submit data (such as a foreign holiday of which we were not aware) we will remind them to inform us if they will not be able to submit data. If the lack of data was due to non-adherence to the study protocol and if the participant fails to submit data for more than 20% of a subsequent 28-day period they will be withdrawn from the study. If the participant does not wish to proceed with the study at any stage they will be withdrawn and this will have no adverse effect on their routine care.

In addition to recording their symptoms and spirometry, subjects receiving home monitoring will be asked to test a urine sample once every week and send a urine sample in a prepaid envelope. These samples will be batched and subsequently analysed for biomarker analysis and this data will not be used by the research team during the course of this study.

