### Secondary outcome measures

**Antibiotic requirements** will be measured by total number of completed days on oral and intravenous antibiotics.
**Protocol defined pulmonary exacerbations** will be recorded using the modified Fuchs criteria [18], which requires the presence of 4 or more of the following criteria:· Change in sputum· New or increased haemoptysis· Increased cough· Increased dyspnoea· Malaise, fatigue, or lethargy· Temperature above 38 °C· Anorexia or weight loss· Sinus pain or tenderness· Change in sinus discharge· Change in physical examination of the chest· Decrease in pulmonary function by 10%· Radiographic changes indicative of pulmonary infection

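### Exacerbations, a secondary outcome, are ascertained unequally by arm in a non-blinded trial, so the between-arm count may be shifted by detection

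*Protocol article*

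**What the plan says.** The two arms are followed differently between study visits.

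- **Monitored arm (Home monitoring group).** "Participants will be asked to record their FEV_1_ using a digital spirometer twice weekly (Monday and Thursday"). Symptoms are scored on the same days with the CFRSD-CRISS, a tool "designed to detect symptoms of pulmonary exacerbations in CF, taking around 5 min to complete". An email alert fires on "a drop in FEV_1_ of 10% or more from baseline", or when the symptom score worsens by more than three points. Then: "Following an email alert, the CF team will contact the participant within 24 h to discuss their symptoms". Clinic assessment follows if needed. The section adds: "If prescribed antibiotics, we will document whether these were prescribed for a protocol-defined pulmonary exacerbation (see definition below").
- **Control arm (Routine care group).** Usual outpatient appointments, with admission when required. No home readings, alerts or prescription-level check are described.
- **Both arms.** According to the abstract, "pulmonary exacerbations (defined by the modified Fuchs criteria) are recorded at each study visit". Outcome measures gives the visits as baseline, 3, 6, 9 and 12 months.
- **Definition (Secondary outcome measures).** Four or more of 12 modified Fuchs criteria, one of which is "Decrease in pulmonary function by 10" per cent. The list names neither the spirometer nor the reference value for that criterion.

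Study design calls the trial non-blinded. Background cites an earlier randomised pilot in which "home monitoring was able to detect more pulmonary exacerbations than standard care".

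**The concern.** Exacerbations are a listed secondary outcome, and their frequency is among the effects the abstract says the study will assess. A between-arm count can be interpreted only if an episode of given severity has about the same chance of being recorded in either arm. Here one arm has twice-weekly surveillance, prompted contact and a check of prescriptions against the definition. The other, as described, has none of these between visits.

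A mild episode could therefore be recorded in a monitored patient and missed in a control. That would push the monitored count up, and a true reduction could be hidden or reversed in appearance. The overlap between an alert trigger and a criterion could add to this if home readings are accepted as evidence.

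This is a matter of data collection. If the criteria are not documented when a control starts antibiotics, no later analysis can restore them.

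**Working it through.** **1. The plan's own figure.** None is given for exacerbations. The only precision statement (Sample size) concerns bed days: half-width = 1.96 × 10/√40 = 3.10, so 42 ± 3.10 = (38.9, 45.1) and 36 ± 3.10 = (32.9, 39.1). This agrees with the stated (39, 45) and (33, 39). Only the 40 per arm is used below.

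**2. Ascertainment side by side.**

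| Step | Monitored | Control |
|---|---|---|
| FEV1 and symptom score between visits | twice weekly | none described |
| Contact prompted by deterioration | within 24 h of an alert | none described |
| Prescription checked against the definition | described | not described |
| 3-monthly study visits | yes | yes |
| Routine clinic and admissions | yes | yes |

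**3. Scheduled looks.** After the 2-week run-in, 50 weeks × 2 = 100 home readings, against 4 post-baseline study visits: 100/4 = 25. Routine clinic visits and admissions are left out because their number is not given, so 25 overstates the contrast in total contacts.

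**4. Chances to meet the FEV1 criterion, if home readings count.** Assumptions (not in the article): no true change, independent normal errors, baseline the mean of 4 readings (2 weeks × 2), and the within-person coefficient of variation shown.

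| Coefficient of variation | At least one 10% fall in 100 readings | In 4 visits |
|---|---|---|
| 3% | 9% | 0.5% |
| 4% | 49% | 4% |
| 5% | 79% | 12% |
| 6% | 92% | 22% |

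These are chances of meeting one criterion by noise, not of having an exacerbation.

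**5. Effect on the rate ratio (monitored/control).** Let d be control capture divided by monitored capture. Apparent ratio = true ratio / d. The range of d is assumed.

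| d | True ratio 1.0 appears as | True ratio 0.8 appears as |
|---|---|---|
| 0.7 | 1/0.7 = 1.43 | 0.8/0.7 = 1.14 |
| 0.8 | 1/0.8 = 1.25 | 0.8/0.8 = 1.00 |
| 0.9 | 1/0.9 = 1.11 | 0.8/0.9 = 0.89 |

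**6. Could such a shift look like a finding with 40 per arm?** Use a Wald test on the log rate ratio, with SE = √[(1/m1 + k)/40 + (1/m0 + k)/40], where m1 and m0 are true rate × capture in the monitored and control arms. Assume equal true rates of 2 to 4 per year, k = 0 (Poisson) or 0.3 (overdispersed), and 90% capture in the monitored arm.

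- Control capture 80% (d = 0.89): apparent ratio 0.9/0.8 = 1.125; chance of significance about 9% to 16%.
- Control capture 70% (d = 0.78): apparent ratio 0.9/0.7 = 1.29; about 21% to 51%.

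Worked case for the second line, rate 2 and k = 0: m1 = 1.8, m0 = 1.4, SE = 0.178, log ratio = 0.251, z = 1.41, giving 29% against a nominal 5%. The article plans basic two-group tests rather than this one, so the figures show scale only.

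**The case against.** The case on the other side is substantial.

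- **The definition and the visit schedule are common to both arms.** The routine-care section is one sentence about care, not data collection, and an article may leave a control-arm form to the full protocol. That is possible. But the article does describe the check, and places it under one arm; the unequal surveillance is explicit.
- **Home readings may not count.** Outcome spirometry is described as a clinic measurement, and home FEV1 as an alert signal leading to contact and, if needed, assessment. The article leaves this open, so the overlap is a risk, not an established fault.
- **An alert is not an event.** Four of 12 criteria are needed, and most are symptoms or clinical findings. This stands, and it limits what the FEV1 overlap can do alone.
- **Earlier detection is the purpose of the intervention.** The stated hypothesis concerns bed days and quality of life, and group tests are labelled exploratory in a self-described pilot. More recorded exacerbations with fewer bed days would fit the rationale. This stands. The fault lies in the unequal counting, not in the monitoring.
- **The capture range has no source in the article.** Correct; it is an illustration.

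A reader might also infer that controls cannot meet the 10% criterion, or that their events rest on patients' recall. The text supports neither. Controls have spirometry at study visits and attend clinic and admissions, so their chance is lower but not nil. The source used for visit recording is not stated, and in a single-centre trial at the CF centre it could be clinic records.

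**Conclusion.** The concern holds in a limited form. As the article is written, a listed secondary outcome is ascertained more intensively in one arm of a non-blinded trial, and the antibiotic-prescription check is described for that arm only. The comparison may be shifted toward more recorded events with monitoring, and a benefit could be masked.

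It is tempting to go further and say that the monitored arm will show more exacerbations. The article does not support that: early treatment, the aim of the intervention, could lower the count, so the net direction and size are not determined. The shift from 1.0 to between 1.11 and 1.43 rests wholly on assumed relative capture of 90% to 70%, and the false-signal figures also rest on assumed event rates and dispersion.

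Bed days, a primary outcome, do not depend on detecting a diagnosis in the same way. The point is therefore worth correcting, but it does not put the main comparison at risk through this route.

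**What to change.** Three changes to outcome recording, none to treatment:

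1. Complete the same modified Fuchs form at every antibiotic start in both arms, wherever it occurs (clinic, telephone or admission), and make antibiotic-treated episodes meeting the criteria the compared endpoint.
2. State that only clinic spirometry counts toward the 10% criterion in the between-arm comparison.
3. Report alert-detected, untreated events for the monitored arm only, as description.

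The cost is a short extra form for controls, at antibiotic courses the study already records, plus protocol wording. Some mild monitored-arm events leave the comparison.

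This equalises documentation, not surveillance. Alerts can still lead to more antibiotic starts in one arm, so some detection bias remains. The exacerbation count should be read beside antibiotic days and inpatient bed days, and the report should say so.
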